### Study assessments

2.4

All three arms will involve structured assessments at baseline, every 2 weeks until week 8, followed by monthly assessments up to month 6 to measure symptom severity, quality of life, functional capacity, adverse events, and adherence (see **figure 2** for a detailed overview of assessment schedules across all visits). The study will involve a detailed medical history, including sociodemographics, medical and psychiatric history, and previous and current medication. Clinical symptoms related to depression, trauma, and sleep are assessed using the test procedures described below.

**Figure 2 f2:**
[figure not shown]
Overview of study procedures and study visit.

Ayurvedic data, i.e. prakṛti (constitution), agni (state of digestion and metabolism), koṣṭha (sensitivity of bowel), various parīkṣā (examinations) i.e. āturabala pramāṇa, jihvā, nādi, manaha parikṣā, nidāna pañcaka specifically for viśada and manas bhāva parīkṣā will be assessed of all the patients of Ayurveda group and combination group. These all will be assessed by using specific proforma. This proforma contains all above data in detailed as per the classical references. The recording of Ayurvedic parameters enables a comprehensive classification of the Ayurvedic definition of depression and the derivation of therapeutic measures.

#### Description of study scales

2.4.1

Columbia-Suicide Severity Rating Scale (C-SSRS (19)) is a validated, standardized, and widely adopted tool for assessing suicidal ideation and behaviours, with strong predictive validity and global clinical and research applications.

The Montgomery-Åsberg Depression Rating Scale (MADRS (20)) is developed to diagnose depression. The ratings should be based on a clinical interview moving from broadly phrased questions about symptoms to more detailed ones which allow a precise rating of severity. The scale is reliable and valid and sensitive to change in the depressive symptoms.

The Hamilton Depression Rating Scale (HAM-D (21)) is a widely used clinician-administered instrument for assessing the severity of depressive symptoms in adults. It’s a structured interview-based scale that provides a quantitative measure of the patient’s current depressive state. The scores for all items are summed to produce a total score, which reflects the overall severity of depression. The most commonly used version is the 17-item version (HAM-D-17, REF).

The Patient Health Questionnaire-9 (PHQ-9 (22)) is a widely used self-report measure designed to assess the severity of depressive symptoms in adults. It’s a brief, reliable, and valid instrument frequently employed in clinical practice , research settings, and screening for depression. The PHQ-9 is a simple questionnaire where individuals rate the severity of each symptom on a four-point scale. The scores for each symptom are summed to produce a total score ranging from 0 to 27. Higher scores indicate greater symptom severity.

The Pittsburgh Sleep Quality Index (PSQI (23)) is a self-rated questionnaire designed to measure sleep quality and disturbances over a one-month period. Higher scores indicating poorer sleep quality.

The abbreviated version of the Childhood Trauma Questionnaire (CTQ-SF (24)) consists out of 28 items that describe situations while growing up. Items can be answered with “never true”, “rarely true”, “sometimes true”, “often true” or “very often true”. Bernstein et al. (24) tested this short version of the CTQ against the longer version and concluded that the scale demonstrated good criterion-related validity and that the same meaning across study samples was measured. To keep the time invested in the current study to a minimum, while obtaining all relevant data, the CTQ-SF was chosen. The average administration time is around 10 minutes.

The General Assessment of Side Effects (GASE (30)) consists of 36 items (symptom descriptions) organized by body parts. GASE collects information on symptoms experienced during the past week. These symptoms can be rated as “not present”, “mild”, “moderate,” or “severe.” In the current study, the subject rates the symptoms and the doctors rate the relatedness. The symptoms are noted as adverse event when the doctor rates the symptom as clinically significant. The GASE also requests to report symptoms not listed (spontaneous). When noted as adverse event, the doctor will also rate the severity and relatedness to medication. The GASE has high internal consistency, which indicates good reliability and is validated. The mean administration time is 5–10 minutes.

The Medication Adherence Report Scale – 5 items (MARS−5 (31, 32)) is a self−report questionnaire designed to assess both intentional and unintentional non-adherence to medication regimens. It is a condensed version of the original 10−item scale (MARS−10) developed by Rob Horne et al.

The Work Productivity and Activity Impairment (WPAI (33)) questionnaire is a self-report measure designed to assess the impact of health conditions on work productivity and activity impairment. It’s frequently used in clinical trials and research studies to quantify the effect of illnesses, including mental health disorders like depression, on various aspects of an individual’s work and daily life.

The Functional Assessment Short Test (FAST (34)) is a brief, clinician-administered instrument designed to assess the level of functional impairment in individuals with mental illness. It’s a useful tool for evaluating the impact of a mental health condition on various aspects of a person’s daily life, providing a quantitative measure of functional capacity. The FAST assesses functional impairment across the key domains Social Functioning, Occupational Functioning, Self-Care Functioning and Home-Living Functioning. A trained clinician administers the FAST, typically through an interview with the patient.

The Global Assessment of Functioning (GAF (35)) scale was a numerical scale used in psychiatry to rate a person’s overall level of psychological, social, and occupational functioning. Scores ranged from 0 to 100, with higher scores indicating better functioning and lower scores reflecting more severe impairment.

The Perceived Deficit Questionnaire (PDQ-5 (36)) was developed specifically for multiple sclerosis to provide a self-report measure of cognitive dysfunction. This instrument provides an assessment of several domains of cognitive functioning that are frequently affected in multiple sclerosis, as well as in psychotic and affective disorders: attention, retrospective memory, prospective memory, and planning and organization. From the full-length PDQ version, a short version with 5 items was created and validated. The PDQ-5 includes items from all 4 PDQ-20 subscales (attention/concentration, retrospective memory, prospective memory, planning/organization).

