#### Arm C: combination treatment arm

2.3.3

Patients who are treated at the Ayurvedic hospital but have previously received allopathic treatment will continue to receive allopathic treatment and start new ayurvedic treatment. This arm integrates Allopathic and Ayurvedic treatments, collaboratively managed by both a Psychiatrist and an Ayurvedic specialist. The treatment strategy will be individualized, considering both the patient’s clinical presentation and preferences.

A patient who is already on Allopathic medication (antidepressants) from their psychiatrist and wishes to start ayurvedic treatment would be categorized into this group. The Ayurvedic specialist and the patients treating Psychiatrist would collaboratively decide whether to maintain, reduce, or discontinue the Allopathic medication as the Ayurvedic treatment progresses. If no Allopathic treatment has been initiated, Ayurvedic treatment will be administered for eight weeks before a joint clinical decision is made regarding the addition of allopathic medication. This approach aims to leverage the potential synergistic effects of both treatment modalities, promoting personalized and effective management of MDD. Previous studies have shown that allopathic psychiatric medication can be combined safely with Ayurvedic treatments such as herbs (10, 11, 16–18).

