### Ethical considerations and data protection

2.8

Ethical considerations will guide all aspects of the study, from design and implementation to data analysis and dissemination. The research protocol was approved by the relevant Institutional Ethics Review Boards (IERBs) at participating institutions (MAM University approval number: MAM UNI/IECHR/2025; Bhaikaka University approval number: IEC/BU/162/Faculty/25/135/2025). In addition, the study was pre-registered with the Indian authorities (CTRI/2025/07/090147).

All potential participants will receive comprehensive information about the study’s purpose, procedures, risks, and benefits ensuring that participants can make an informed decision about their participation. Written informed consent will be obtained from all participants prior to any study procedures being undertaken. Participants will be free to withdraw their consent and discontinue their participation at any time without penalty. Participants will be closely monitored for the occurrence of adverse events throughout the study period. Regular follow-up visits will allow for the detection and assessment of any adverse effects, whether related to the study interventions or other factors. If any adverse events occur medical attention, adjustments to the treatment regimen, counselling, or other supportive measures as needed appropriate interventions will be provided promptly. Serious adverse events will be reported immediately to the relevant IERBs and the study team. The study will have a clear protocol for managing adverse events. A data safety monitoring board will regularly review safety data to ensure participant safety. The study’s data management procedures will strictly adhere to relevant data protection regulations, which includes GDPR Compliance, Indian Data Protection Standards, Local Data Safety Standards and Data Anonymization.

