The choice of statistical test will depend on the nature of the data and the specific research question. For continuous outcome variables (e.g., scores on depression rating scales, quality of life scores, continuous physiological measures), Analysis of Variance (ANOVA) or independent samples t-tests will be used to compare means between the three treatment groups (Ayurvedic-only, Allopathic-only, and Combination). *Post-hoc* tests (e.g., Tukey’s HSD, Bonferroni correction) will be employed if significant differences are found between groups to determine which specific groups differ significantly. For categorical outcome variables (e.g., presence or absence of adverse events, categorical measures of quality of life, treatment adherence categories), Chi-square tests or Fisher’s exact tests (for small sample sizes) will be used to compare proportions between treatment groups. Given the repeated measures design (baseline, 8 weeks, 3 months, 6 months), appropriate statistical models for longitudinal data (e.g., repeated measures ANOVA, mixed-effects models) will be used to analyse changes in outcome measures over time within each treatment group and to examine the interaction effects between treatment group and time. This will allow for a more powerful examination of treatment effects and the assessment of treatment response trajectories. Strategies to address missing data will be carefully considered and documented. In addition to p-values, effect sizes (e.g., Cohen’s d) and 95% confidence intervals will be reported for all significant findings. All statistical analyses will be performed using appropriate statistical software packages (e.g., SPSS, R).

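### The stated adverse-event rule has no new-or-worsened condition, and the between-arm comparison has no stated baseline or relatedness filter, so pre-existing symptoms can enter it

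*Protocol article*

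**What the plan says.** All of this is in the protocol article.

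- **Capture (2.4.1, GASE).** "GASE collects information on symptoms experienced during the past week". The window is not tied to the start of treatment.
- **Rule (2.4.1, GASE).** "The symptoms are noted as adverse event when the doctor rates the symptom as clinically significant".
- **Attribution (2.4.1, GASE).** Relatedness is rated: "In the current study, the subject rates the symptoms and the doctors rate the relatedness", and again "When noted as adverse event, the doctor will also rate the severity and relatedness to medication".
- **Scope (2.8).** Monitoring covers adverse effects "whether related to the study interventions or other factors".
- **Objective (1.2).** The aim is to compare the incidence, type and severity of adverse events associated with the treatments.
- **Analysis (2.9).** Chi-square or Fisher's exact tests compare proportions between arms. The example of a categorical outcome is "presence or absence of adverse events".
- **Baseline (2.4).** "All three arms will involve structured assessments at baseline, every 2 weeks until week 8". Adverse events are among the things these assessments measure.
- **Treatment at entry (2.2.1, 2.3.3).** Earlier treatment in the current episode is allowed in every arm. On Arm C: "A patient who is already on Allopathic medication (antidepressants) from their psychiatrist and wishes to start ayurvedic treatment would be categorized into this group".

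**The concern.** Every participant has moderate or severe depression, so clinically significant symptoms before the first study treatment are to be expected. Some participants also enter with side effects of earlier or continuing treatment. Under the stated rule, a symptom of either kind that persists to a post-baseline visit qualifies as an adverse event just as a newly arising one does. The presence-or-absence comparison does not say that such symptoms are set aside.

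The resulting proportion is a prevalence of clinically significant symptoms, not an incidence of events. Two errors can follow. If symptoms at entry are about equally common in the arms, a real difference in new events is diluted. If they differ between arms, as is plausible when the arms are formed by preference, hospital and treatment history, a difference can appear where new-event risks are equal. The comparison of side effects is one of the two aims stated in the abstract, so this affects a result that readers will look for.

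**Working it through.** The plan gives no adverse-event rate, so there is no figure of its own to reproduce. The check has two parts.

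**1. Following one symptom through the text.** Take a symptom that is present at baseline, unchanged at week 4, and rated clinically significant.
- The GASE rule in 2.4.1 notes it as an adverse event. No onset or worsening condition stops it.
- The relatedness rating then applies. A symptom judged to be part of the depression can be rated unrelated. A continuing antidepressant side effect in Arm C can properly be rated related to medication, because the rating does not say which treatment is meant.
- The comparison in 2.9 uses presence or absence and names no filter on relatedness or on baseline status.
- Result: the symptom can enter the comparison although nothing new has occurred.

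**2. Size, on assumed rates.** Let *b* be the share of an arm with a clinically significant symptom at entry that is later counted, and *e* the risk of a new or worsened event. Assuming the two are independent, the observed proportion is

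P = 1 − (1 − b)(1 − e).

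*Dilution (equal b).* The observed difference is (e₂ − e₁)(1 − b).
- With b = 60%, e = 20% and 40%: P = 1 − 0.4 × 0.8 = 68% and 1 − 0.4 × 0.6 = 76%. A true 20-point difference becomes 0.20 × 0.4 = 8 points.
- With e = 10% and 30%, 35 per arm (section 2.1) and an assumed two-sided 5% level (normal approximation):

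| b in both arms | Observed proportions | Difference (points) | Power |
|---|---|---|---|
| 0% | 10% vs 30% | 20 | 55% |
| 30% | 37% vs 51% | 14 | 22% |
| 50% | 55% vs 65% | 10 | 13% |
| 70% | 73% vs 79% | 6 | 8% |

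*Spurious difference (equal e, unequal b).* The observed difference is (1 − e) times the difference in b.
- With e = 20% and b = 40% vs 60%: P = 1 − 0.6 × 0.8 = 52% and 1 − 0.4 × 0.8 = 68%, a 16-point difference with no true one.
- With e from 10% to 30% and b = 30% in one arm against 50% to 60% in the other: 14 to 27 points, significant in about 22% to 62% of studies instead of 5%.
- With b = 50% vs 70% over the same range of e: 14 to 18 points, significant in about 25% to 35%.

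The sign depends only on which arm has the higher b, and the document does not say which that is.

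**The case against.** **Attribution is planned.** The doctor rates relatedness, so recording an event and attributing it to treatment are separate steps. This stands against a stronger reading that a reader might infer: that depressive symptoms and old antidepressant side effects are counted as harms of the study treatment. The text does not say so. It does not remove the narrower point, because the comparison in 2.9 does not state that it uses the rating, and the rating does not separate a continuing antidepressant from newly started Ayurvedic treatment.

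**Baseline is used elsewhere.** The abstract plans comparisons of secondary outcomes with baseline, 2.9 adds longitudinal models, and 1.2 speaks of incidence. This is fair for scale scores. It does not define which adverse events count as present, and the word incidence makes the mismatch with the stated rule plainer.

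**Arm C is not unique.** Section 2.2.1 admits previously treated patients to any arm, and 2.3.3 also describes patients for whom no allopathic treatment has been initiated. Continuing allopathic care is itself part of the combination. All of this stands, so an inflated Arm C rate cannot be asserted as fact. Carry-over is only most characteristic of that arm.

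**A new-or-worsened derivation is often left to the analysis plan.** True, and the full protocol may contain one; the visit schedule in Figure 2 is also not visible. But the article is not silent. It states an operating rule which, followed as written, does not yield the quantity named in the objective.

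**Conclusion.** The point holds in limited form. The stated rule lacks a new-or-worsened condition and the planned comparison states no baseline or relatedness filter, so symptoms that predate study treatment can enter it. It then estimates prevalence rather than the incidence named in 1.2.

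The size and direction are unknown. The illustrations rest on assumed rates, on independence of entry symptoms and new events, and on every entry symptom in *b* being counted later. If doctors in practice decline to note unchanged symptoms, or if the analysis is restricted to related events, the effect is smaller. In Arm C the relatedness restriction would not be sufficient. Side effects are a secondary, exploratory outcome and the article calls its findings hypothesis-generating, so this is a definition that should be corrected, not a threat to the primary endpoint.

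**What to change.** 1. Keep the clinical-significance requirement. For the between-arm comparison, count only events that are absent at baseline or of higher severity than at baseline, plus unlisted events that start after the first study treatment. Use the scheduled baseline assessment, and confirm that the GASE is administered then.
2. Report the baseline prevalence of clinically significant symptoms by arm beside that comparison. Ongoing baseline side effects are described there and not counted as incident events.
3. Record relatedness separately for allopathic and for Ayurvedic treatment.
4. State that, for Arm C patients already on antidepressants, new-or-worsened events describe the period after Ayurvedic treatment is added. They are not the incidence for the combination counted from the start of the antidepressant.

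Cost: a sentence of definition, one variable derived from assessments already scheduled, and one extra relatedness field in the eCRF. Continuing side effects in Arm C move from the test to the descriptive table.

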### Hypothesis and objectives

1.2

Based on the published literature, we assume that allopathic and Ayurvedic treatments are equally effective in treating depression, both leading to improvements in symptom severity. Therefore, we do not expect any statistically significant difference in treatment effect between the treatment groups (between-group effect) in week 8. However, we hypothesize that both therapies will lead to an improvement in depression symptoms over a period of 8 weeks (within-group effect). The question is exploratory in nature due to the design and methodology.

This study will pursue the following scientific objectives:

Treatment Effect: To quantitatively compare the effect of allopathic and ayurvedic treatments (and their combination) in reducing the severity of depressive symptoms in MDD, as measured by validated rating scales (primary Montgomery-Åsberg Depression Rating Scale (MADRS), secondary Hamilton Depression Rating Scale (HAM-D) and Patient Health Questionnaire-9 (PHQ-9) at baseline, 8 weeks, 3 months and 6 months.Side Effects and Quality of Life: To compare the incidence, type, and severity of adverse events associated with allopathic and ayurvedic treatments using standardized adverse event reporting like Udvalg for Kliniske Undersøgelser Scale (UKU), General Assessment of Side (GASE) and Medication Adherence Report Scale (MARS). Furthermore, to assess differences in quality of life (QoL) and daily functioning between treatment groups using validated QoL instruments (e.g., WHOQOL-BREF) and functional assessment scales (e.g., Global Assessment of Functioning (e.g., Global Assessment of Functioning (GAF) and Functional Assessment Short Test (FAST).General Health Evaluation: To evaluate and compare changes in general health parameters (e.g., Body Mass Index (BMI), vital signs, relevant blood work indicators such as liver and kidney function tests, electrolytes, CRP, leukocytes, red blood cells, platelets, haemoglobin , haematocrit , red cell indices and TSH) across treatment groups over the study duration.

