### Study intervention

2.3

This study will utilize a naturalistic observational design, leveraging the established expertise and practices of two distinct clinical settings: Nadiad Ayurveda Hospital (for Ayurvedic only and combined treatments) and Shree Krishna Hospital, Department of Psychiatry, Bhaikaka University, Karamsad, Anand (for allopathic treatments). The assignment to the groups follows a clear system. The two hospitals have different areas of focus. One clinic (Shree Krishna Hospital) provides exclusively allopathic treatment, while the other (Nadiad Ayurveda Hospital) provides Ayurvedic treatment. Patients who are treated at the Ayurvedic hospital but have previously received allopathic treatment will continue to receive allopathic treatment (combined therapy). The clinic is selected based on clinical indications and in consultation with the patient.

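### Adverse events taken from GASE depend on a doctor's judgement of clinical significance, and Arm A is at a different hospital from Arms B and C, so the A-vs-B and A-vs-C comparisons are open to differential ascertainment

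*Protocol article*

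**What the plan says.** Section 1.2 (Hypothesis and objectives) sets the aim "To compare the incidence, type, and severity of adverse events associated with allopathic and ayurvedic treatments", using instruments such as UKU, GASE and MARS. Section 2.7 lists the same instruments as exploratory secondary outcomes for side effects.

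Section 2.4.1 (Description of study scales) gives the route from symptom to event for GASE:
- Symptom ratings come from the patient, while judging relatedness falls to the doctors.
- The step from symptom to event is a doctor's decision: "The symptoms are noted as adverse event when the doctor rates the symptom as clinically significant".
- Further ratings follow for those events: "When noted as adverse event, the doctor will also rate the severity and relatedness to medication".

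Section 2.9 gives "presence or absence of adverse events" as an example of a categorical outcome, for which Chi-square or Fisher's exact tests "will be used to compare proportions between treatment groups".

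Section 2.3 (Study intervention) ties arm to hospital: "One clinic (Shree Krishna Hospital) provides exclusively allopathic treatment, while the other (Nadiad Ayurveda Hospital) provides Ayurvedic treatment". The combined treatment is also given at the Ayurvedic hospital. Under sections 2.3.1 to 2.3.3, treatment is overseen by a psychiatrist in Arm A, by an Ayurvedic specialist in Arm B and by both in Arm C.

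**The concern.** An incidence comparison needs the same definition of an event in every group. Here a GASE symptom becomes an event through a judgement for which the article prints no common criterion. For A vs B and A vs C, the patients being compared are at different hospitals that work in different medical systems. If doctors at one hospital call a symptom clinically significant more readily than doctors at the other, adverse-event rates will differ even when patients experience the same symptoms. The reverse can also happen: a real difference can be hidden. Severity and relatedness are rated by the doctor once the event is noted, so they inherit the same dependence.

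The abstract promises comparative evidence on side effects to inform practice. What is at stake is whether a difference in adverse-event rates, or the lack of one, says anything about the treatments.

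**Working it through.** The article states no figure for adverse events, so there is none to reproduce. The check has two parts.

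**1. Can the two sources of difference be separated?**

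| Contrast | Hospitals | Overseeing clinicians | Labelling threshold |
|---|---|---|---|
| A vs B | different | psychiatrist vs Ayurvedic specialist | fully aliased with arm |
| A vs C | different | psychiatrist vs both | fully aliased with arm |
| B vs C | same | Ayurvedic specialist vs both | less affected |

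In the first two contrasts hospital and arm are the same variable. A hospital term in a model either cannot be estimated or takes the treatment effect with it.

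**2. How large could the effect be?**

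From the article: about 35 patients per arm (section 2.1) and a Chi-square or Fisher's exact test (section 2.9).

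Assumed, with no source in the documents: true incidence of 60% in both arms, the flagging probabilities below, and a two-sided test at 0.05.

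Formula: observed incidence = true incidence × probability that the doctor flags the symptom. For example, 0.60 × 0.70 = 0.42 and 0.60 × 0.40 = 0.24.

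The chance of p < 0.05 was found by summing the binomial probabilities over all 36 × 36 possible outcomes with 35 patients per arm (Chi-square without continuity correction).

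| Flagging | Observed incidence | Observed ratio | Chi-square | Fisher |
|---|---|---|---|---|
| 70% vs 70% | 42% vs 42% | 1.00 | 5% | 3% |
| 70% vs 60% | 42% vs 36% | 0.86 | 8% | 5% |
| 60% vs 40% | 36% vs 24% | 0.67 | 20% (19.5%) | 13% |
| 70% vs 40% | 42% vs 24% | 0.57 | 37% | 28% |

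Other assumptions give the same picture. At 50% true incidence, flagging of 80% vs 60% gives 14% by Chi-square and 10% by Fisher. Flagging of 80% vs 40% gives 45% and 36%.

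With equal true incidence p, the observed ratio is (p × s2)/(p × s1) = s2/s1, where s1 and s2 are the flagging probabilities at the two hospitals. It does not depend on sample size, so more patients would only make the false difference more significant.

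Masking follows from the same formula. True incidences of 70% and 40%, flagged at 40% and 70%, give 0.70 × 0.40 = 0.28 and 0.40 × 0.70 = 0.28, so no difference is seen.

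**The case against.** Several points on the other side stand and limit the concern.

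- **The gate is not said to be the only route.** The article describes it for GASE. Section 2.8 also has adverse events detected at follow-up visits, under a handling protocol that is not shown. UKU does not pass through this gate, although it is clinician-administered and so does not avoid rater differences. A reader might infer that a symptom counts only if a doctor calls it significant; the text does not say so.
- **The rater is not identified.** Section 2.4.1 says only that a doctor makes the rating. A reader might infer an unblinded treating doctor. That is plausible given the set-up, but the sections on the arms describe who oversees treatment, not who rates GASE.
- **GASE is already a named side-effect outcome.** The patient-rated data are therefore collected. The article does not say which GASE variable carries the main comparison, and leaving that to a fuller document is not in itself an error.
- **Common training is planned.** Section 2.6 provides manuals, practice sessions and a competency check. This could narrow a gap between hospitals, but nothing printed addresses the clinical-significance judgement. The safety board in section 2.8 is not described as re-judging events.
- **The flagging gaps are assumptions.** With a 10-point gap the inflation is small: 8% by Chi-square, and by Fisher no more than the nominal 5%.
- **The outcome is exploratory.** The study calls itself hypothesis-generating, and section 3.2 admits confounding, selection bias and heterogeneity of interventions. It does not name outcome ascertainment.

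None of this removes the core problem. The event definition and the between-group test are both printed, and an analysis plan cannot recover a common threshold from events already filtered at each hospital.

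**Conclusion.** The concern holds for A vs B and A vs C. Adverse-event presence taken through the GASE route can differ between these arms because of labelling practice alone, and no adjustment for hospital can separate that from treatment. B vs C is less affected, because those arms share a hospital and differ in the psychiatrist's involvement.

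The documents show an exposure to bias, not its size or direction. The range of 8% to 37% (Chi-square) or 5% to 28% (Fisher) rests on the assumed 60% true incidence and flagging gaps of 10 to 30 points. A reader might go further and conclude that the side-effect comparison is already biased, or favours one system of medicine; nothing in the article supports that. The consequence is confined to an exploratory secondary outcome, but it should be dealt with, because the remedy is cheap and the article promises comparative side-effect evidence.

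**What to change.** 1. State that the main between-arm side-effect comparison uses the patient-rated GASE before any doctor's filter. Use two summaries: the total score adjusted for baseline, and any new or worsened symptom since baseline. Both should count symptoms regardless of the doctor's rating of significance or relatedness.
2. Report doctor-noted adverse events beside it, by arm and hospital, and say that A-vs-B and A-vs-C differences in these events will not be read as treatment differences.
3. Add differential ascertainment of adverse events to the limitations in section 3.2.

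The cost is mainly wording, since GASE is already collected. There is a real downside to state. Self-ratings include depressive complaints, which baseline adjustment only partly handles. They may also reflect the expectations of patients who know and chose their treatment, which baseline adjustment does not remove. The patient-rated comparison takes out the hospital-specific doctor filter; it does not make the comparison free of bias. Common written criteria for clinical significance at both hospitals would help the doctor-noted events as well.
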